## **Conformity Declaration**

This document is a protocol for a research project. This study will be conducted in accordance with all the stipulations of this protocol, the current regulations of the CEP/CONEP System and the guidelines established by the Document of the Americas and the Guide for Good Clinical Practice (E6/R2) of the ICH - International Council for Harmonization of Technical Requirements for Pharmaceuticals for Human Use.

## SYNOPSIS

|                                                             |                                                                                                                                                                                                                                                                                                                                                                                                                                                                               |
|-------------------------------------------------------------|-------------------------------------------------------------------------------------------------------------------------------------------------------------------------------------------------------------------------------------------------------------------------------------------------------------------------------------------------------------------------------------------------------------------------------------------------------------------------------|
| Title                                                | Halofuginone for adult patients with SARS-CoV-2: Multicentre, phase 2, randomized, double-blind, placebo-controlled clinical trial.                                                                                                                                                                                                                                                                                                                                           |
| Public title                                         | HALOfuginone for SARS-CoV-2: HALOS trial                                                                                                                                                                                                                                                                                                                                                                                                                                      |

| Principal Sponsor                                    | Associação Beneficente Síria - HCor                                                                                                                                                                                                                                                                                                                                                                                                                                           |
| Financial support                                    | CoviCept Therapeutics                                                                                                                                                                                                                                                                                                                                                                                                                                                         |
| Health condition(s) or problem(s) studied:           | SARS-CoV-2 infection                                                                                                                                                                                                                                                                                                                                                                                                                                                          |
| Study design                                         | Multicentre, phase 2, randomized, double-blind, placebo-controlled clinical trial.                                                                                                                                                                                                                                                                                                                                                                                            |
| Objective                                            | To evaluate the effectiveness of the use of halofuginone in the decay rate of the SARS-CoV-2 viral load logarithmic curve obtained via nasopharyngeal swab between baseline, fifth and tenth day after randomization.                                                                                                                                                                                                                                                         |
| Eligibility                                          | Inclusion Criteria: 
 
1. Adult patients (age <math>\geq 18</math> years);
 
2. COVID-19 diagnosis confirmed by: 
 
a. Detection of SARS-CoV-2 by RT-PCR, or
 
b. Rapid genetic or antigen tests registered by ANVISA;
 
 
 
3. Mild or moderate symptoms without indication for hospitalization;
 
4. Symptoms started seven days ago or less;
 
 |

|  |                                                                                                                                                                                                                                                                                                                                                                                                                                                                                                                                                                                                                                                                                                                                                                                                                                                                                                                                                                                                                                                                                                                                                                                                                                                                                                                                                                                                                                                                                                                                                                               |
|--|-------------------------------------------------------------------------------------------------------------------------------------------------------------------------------------------------------------------------------------------------------------------------------------------------------------------------------------------------------------------------------------------------------------------------------------------------------------------------------------------------------------------------------------------------------------------------------------------------------------------------------------------------------------------------------------------------------------------------------------------------------------------------------------------------------------------------------------------------------------------------------------------------------------------------------------------------------------------------------------------------------------------------------------------------------------------------------------------------------------------------------------------------------------------------------------------------------------------------------------------------------------------------------------------------------------------------------------------------------------------------------------------------------------------------------------------------------------------------------------------------------------------------------------------------------------------------------|
|  | 
5. Be able to access the study's online questionnaire.
 
Exclusion Criteria:
 
 
1. Pregnant or lactating women;
 
2. Known allergy or hypersensitivity to the study drug;
 
3. Patients at high risk of bleeding, defined by: 
 
a. Previous Intracranial hemorrhage,
 
b. Ischemic stroke in the last 3 months,
 
c. Anatomical vascular alteration of the central nervous system known, such as aneurysms or arteriovenous malformations,
 
d. Malignant neoplasm of the central nervous system known,
 
e. Metastatic solid neoplasia,
 
f. Significant closed head or facial trauma in the last 3 months,
 
g. Intracranial abnormalities not listed as absolute contraindications (e.g., benign intracranial tumor),
 
h. Bleeding in the last 2 to 4 weeks (excluding menstrual bleeding),
 
i. Major surgery in the last 3 weeks,
 
j. Current use of full-dose anticoagulants or dual antiplatelet therapy,
 
k. Thrombocytopenia (<100,000/mL) or INR (international standardized ratio) > 1.3;
 
 
 
4. Renal failure, defined as glomerular filtration rate (GFR) estimated by the formulas MDRD or CKD-EPI <30mL/min/1.73m^2;
 
5. Previous participation in the study;
 
6. History of liver disease (cirrhosis) reported by the patient or in medical records, presence of esophageal varices or presence of ascites;
 
 |
|--|-------------------------------------------------------------------------------------------------------------------------------------------------------------------------------------------------------------------------------------------------------------------------------------------------------------------------------------------------------------------------------------------------------------------------------------------------------------------------------------------------------------------------------------------------------------------------------------------------------------------------------------------------------------------------------------------------------------------------------------------------------------------------------------------------------------------------------------------------------------------------------------------------------------------------------------------------------------------------------------------------------------------------------------------------------------------------------------------------------------------------------------------------------------------------------------------------------------------------------------------------------------------------------------------------------------------------------------------------------------------------------------------------------------------------------------------------------------------------------------------------------------------------------------------------------------------------------|

|                                          |                                                                                                                                                                                                                                                                                                                                                                                                                                                                                                                                                |
|------------------------------------------|------------------------------------------------------------------------------------------------------------------------------------------------------------------------------------------------------------------------------------------------------------------------------------------------------------------------------------------------------------------------------------------------------------------------------------------------------------------------------------------------------------------------------------------------|
|                                          | 
7. Decompensated heart failure, defined by the presence of dyspnea attributed to cardiac cause, edema of the lower limbs, crackles on pulmonary auscultation or pathological jugular turgency.
 
8. Participation in other clinical trials with antivirals in COVID-19
                                                                                                                                                                                                                                                             |
| Randomization:                    | Patients will be randomized in a 1:1:1 ratio via an online electronic form available 24 hours a day.                                                                                                                                                                                                                                                                                                                                                                                                                                           |
| Intervention:                     | 
Control:
 
 
• Oral placebo once a daily, for 10 days;
 
 
Interventions:
 
 
• Halofuginone 1mg orally once daily, for 10 days;
 
• Halofuginone 0.5mg orally once daily, for 10 days.
 
                                                                                                                                                                                                                             |
| Data collect                      | Clinical data will be collected from the day of the patient's inclusion in the study on day 1 (baseline) and daily via an online questionnaire filled by the patient until the tenth day. Follow-up calls will be made by the participating center team on the days 14 and 28 to obtain vital status and other clinical data.                                                                                                                                                                                                                  |
| Collection of biological material | Blood collections of the following blood laboratory tests will be performed on the day of inclusion in the study (baseline), and on the tenth day: Complete blood count (CBC), urea, creatinine, alkaline phosphatase, gamma-GT, aspartate aminotransferase, alanine aminotransferase, direct and indirect bilirubin, C-reactive protein, prothrombin time with INR, activated partial thromboplastin time, fibrinogen, sodium and potassium. On the fifth and tenth day, 1 tube will be collected to measure the serum level of halofuginone. |

|                              |                                                                                                                                                                                                                                                                                                                                                                                                                                                                                                                                                                                                                                                                                                                                                                                               |
|------------------------------|-----------------------------------------------------------------------------------------------------------------------------------------------------------------------------------------------------------------------------------------------------------------------------------------------------------------------------------------------------------------------------------------------------------------------------------------------------------------------------------------------------------------------------------------------------------------------------------------------------------------------------------------------------------------------------------------------------------------------------------------------------------------------------------------------|
|                              | Nasopharyngeal swabs for SARS-CoV-2 will be collected on days 1 (baseline), 5 and 10.                                                                                                                                                                                                                                                                                                                                                                                                                                                                                                                                                                                                                                                                                                         |
| Sample size           | A total of 150 patients with confirmed SARS-CoV-2 (50 per arm) have 90% power to detect a drop in viral load via $2.2 \log^{10}$ nasopharyngeal swab from day 1 (baseline) for days 5 and 10 between the intervention and placebo groups                                                                                                                                                                                                                                                                                                                                                                                                                                                                                                                                                      |
| Participating centers | 2 to 5 hospitals in Brazil                                                                                                                                                                                                                                                                                                                                                                                                                                                                                                                                                                                                                                                                                                                                                                    |
| Primary Outcome       | Slope of the logarithmic curve of the SARS-CoV-2 viral load obtained via nasopharyngeal swab between the baseline, fifth and tenth days after randomization.                                                                                                                                                                                                                                                                                                                                                                                                                                                                                                                                                                                                                                  |
| Secondary Outcomes    | 
 
1. Hospital admission between randomization and the day 28;
 
2. Need for invasive mechanical ventilation between randomization and day 28;
 
3. Time to resolve symptoms until the tenth day;
 
4. Ordinal clinical scale of symptoms on 14th (1. not hospitalized, without limitation of daily activities; 2. not hospitalized, with limitation of daily activities; 3. hospitalized, without the need for supplemental oxygen; 4. hospitalized, requiring supplemental oxygen; 5 hospitalized, requiring high-flow nasal oxygen therapy, non-invasive mechanical ventilation, or both; 6. hospitalized, requiring blood oxygenation through a membrane system, invasive mechanical ventilation, or both; 7. Death);
 
 |
| Safety outcomes       | 
 
1. Grade 1, 2, 3 or 4 adverse events, which were not presented when the patient entered the study. Defined by the AIDS division (DAIDS) Table for grading the severity of adult and
 
                                                                                                                                                                                                                                                                                                                                                                                                                                                                                                                                                  |

|                                               |                                                                                                                                                                                                                                                                                                                                                                                                                                                                                                                                                                                                                                                                                                                                                                                                                                                                                                   |
|-----------------------------------------------|---------------------------------------------------------------------------------------------------------------------------------------------------------------------------------------------------------------------------------------------------------------------------------------------------------------------------------------------------------------------------------------------------------------------------------------------------------------------------------------------------------------------------------------------------------------------------------------------------------------------------------------------------------------------------------------------------------------------------------------------------------------------------------------------------------------------------------------------------------------------------------------------------|
|                                               | 
pediatric adverse events (corrected version 2.1, July 2017);
 
 
2. Bleeding 
 
a. Major bleeding,
 
b. Clinically relevant non-major bleeding,
 
c. Minor bleeding;
 
 
 
3. Serious Adverse Event;
 
4. Discontinuation of study drug-related treatment.
 
                                                                                                                                                                                                                                                                                                                                                                                                                                                                                                    |
| Statistical analysis                   | 
The analyses will follow the intention to treat principle. The primary outcome will be a comparison of the viral load logarithm decay rates via RT-PCR to SARS-CoV-2 in 10 days between treatment groups compared to control. A linear mixed model will be used, assuming random intercept and slope for patients. The viral load measurements will be performed 5 and 10 days after randomization.
 
If the RT-PCR exam is not performed for any reason, imputation will be performed using only an estimate via the chain equation method using the mice package. We chose to perform the primary outcome assessment based on multiple imputation methods to correct any viral load values due to loss of information due to mortality, however, based on data by [name] et al. (2020), the expected mortality during the period of exam collection is minimal (<3%).
 |
| Data and security monitoring committee | 
An external and independent data monitoring committee (DMC) will assess safety outcomes and primary outcomes when 60 patients reach the primary assessment of the study outcome. The DMC will
                                                                                                                                                                                                                                                                                                                                                                                                                                                                                                                                                                                                                                                                                              |

|  |                                                                                                    |
|--|----------------------------------------------------------------------------------------------------|
|  | consider safety events to provide a recommendation to continue inclusion or discontinue the study. |
|--|----------------------------------------------------------------------------------------------------|

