#### 3.4.2 Exclusion Criteria

1. Pregnant or lactating women;
2. Known allergy or hypersensitivity to the study drug;
3. Patients at high risk of bleeding, defined by:
  - a. Previous Intracranial hemorrhage,
  - b. Ischemic stroke in the last 3 months,
  - c. Anatomical vascular alteration of the central nervous system known, such as aneurysms or arteriovenous malformations,
  - d. Malignant neoplasm of the central nervous system known,
  - e. Metastatic solid neoplasia,
  - f. Significant closed head or facial trauma in the last 3 months (defined as any trauma that required medical evaluation or hospitalization),
  - g. Known intracranial abnormalities not listed as absolute contraindications (e.g., benign intracranial tumor),
  - h. Bleeding in the last 2 to 4 weeks (excluding menstrual bleeding),

- i. Surgical procedure in the last 3 weeks,
  - j. Current use of full-dose anticoagulants (warfarin, enoxaparin or new anticoagulants) or dual antiplatelet therapy,
  - k. Thrombocytopenia ( $<100,000/\text{mL}$ ) or INR (international standardized ratio)  $> 1.3$ ;
4. Renal failure, defined as glomerular filtration rate (GFR) estimated by the formulas MDRD or CKD-EPI  $<30\text{mL}/\text{min}/1.73\text{m}^2$ ;
  5. Previous participation in the study;
  6. History of liver disease (cirrhosis) reported by the patient or in medical records, presence of esophageal varices or presence of ascites;
  7. Decompensated heart failure, defined by the presence of dyspnea attributed to cardiac cause, edema of the lower limbs, crackles on pulmonary auscultation or pathological jugular turgency.
  8. Participation in other clinical trials with antivirals in COVID-19

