### 3.6 Procedures for verifying the eligibility criteria

After signing the Informed Consent, it will be collected serum creatinine, prothrombin time, platelet count (blood count) and rapid pregnancy tests (in the case of women of childbearing age) to confirm the eligibility criteria. If the patient has underwent part or all the tests in the last 3 days, the results may be considered to verify the eligibility.

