the last 3 weeks, current use of full-dose anticoagulants [warfarin, enoxaparin or new anticoagulants] or dual antiplatelet and platelet therapy to [ $<100,000/\text{mL}$ ] or ISR [international standardized ratio] $> 1.3$ ). It is reinforced that in patients who presented hemorrhagic phenomena, laboratory tests that evaluate coagulation (platelet count and levels of coagulation factors) were not altered, which reinforces the hypothesis that these hemorrhagic phenomena are primarily related to the presence of metastases in these patients.

Absorption of halofuginone after an oral dose was associated with a maximum peak of the drug at  $3.4 \pm 4.8$  hours. About 4-12% of the halofuginone administered was excreted in the urine, mainly in the first 24 hours after administration. Table 3 contains data on the pharmacokinetics of halofuginone in the study doses.

**Table 3.** Pharmacokinetics of halofuginone during the first cycle a

| Dose (mg/day) | C max (ng/mL) | T max (h) | T 1/2 (h) |
|---------------|--------------------------|----------------------|----------------------|
| 0.5           | 0.54                     | 2.8                  | 17.2                 |
| 1             | 0.88                     | 2.0                  | 31.5                 |

a Adapted from de Jong et al.  
Abbreviations: Cmax, plasma peak; Tmax, time to maximum concentration; T1/2, terminal disposal half life

Therefore, in view of the most common adverse events with the use of halofuginone (gastrointestinal symptoms such as nausea and vomiting, which were dependent on the dose administered, as well as duration of cycles), risk of bleeding, as well as pharmacokinetic properties of the drug, if by using doses of 1mg/day and 0.5mg/day in the intervention arms, excluding patients at high risk of bleeding, as well as patients who have less drug elimination.

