There are potential risks related to the use of halofuginone. The main risks are gastrointestinal symptoms such as nausea and vomiting, as well as fatigue. Regarding nausea and vomiting, antiemetics will be prescribed and provided free of charge to patients, following the guidelines of the protocol. Another potential risk of the use of halofuginone refers to a greater chance of bleeding, however, this risk is mitigated by clear and specific criteria and exclusion, not allowing the inclusion of patients with a high risk of bleeding in the study.

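### The platelet limit in exclusion criterion 3k is given per mL, 1,000 times below the evidently intended 100,000/µL

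*Protocol*

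**What the plan says.** The platelet limit appears three times in the protocol, each time per mL.

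- Synopsis, exclusion criterion 3k: below "100,000/mL) or INR (international standardized ratio".
- Section 3.4.2, criterion 3k: "Thrombocytopenia ( $<100,000/\text{mL}$ ) or INR".
- Section 3.10.4, where the dose justification lists the patients excluded for bleeding risk: "dual antiplatelet and platelet therapy to [ $<100,000/\text{mL}$ ] or ISR".

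The limit is never given per µL, per mm³ or as × 10^9/L.

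Two other sections rely on it. Section 3.6 lists the tests taken after consent to confirm eligibility, and these include "platelet count (blood count) and rapid pregnancy tests"; results from the previous three days may be used instead. Section 8.4 acknowledges a possible increase in bleeding with halofuginone and says that "this risk is mitigated by clear and specific criteria and exclusion".

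**The concern.** A platelet limit of 100,000 per mL is not a thrombocytopenia cut-off in any ordinary clinical sense. The figure 100,000 is a familiar cut-off only when counted per µL. As printed, the platelet half of 3k would exclude practically no outpatient; the INR half is unaffected.

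The limit has work to do in the trial. Each patient's count is compared with it at screening, and section 3.9 treats randomising an ineligible patient as a protocol violation. Taken literally, randomising a patient with 50,000/µL would be no violation, and turning that patient away would depart from the text. The protocol gives sites, monitors and anyone programming an eligibility check no correct figure to work from. Whether an automated check exists is not stated, so that last route is a risk and not an established fact.

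What is at stake is a participant safeguard. Section 3.10.4 describes bleeding complications as a concern and reports that 7 of 24 phase I patients bled on the drug. Section 8.4 then points to the exclusion criteria as the mitigation.

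**Working it through.** The plan reports no calculation here, so there is no figure to reproduce. The check is a unit conversion.

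**Inputs**

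- Printed limit: 100,000 per mL (synopsis 3k, section 3.4.2 item 3k, section 3.10.4).
- Conversion: 1 mL = 1,000 µL, and 1 L = 1,000 mL.

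**The limit as printed**

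- 100,000/mL ÷ 1,000 µL per mL = 100/µL.
- 100,000/mL × 1,000 mL per L = 100,000,000/L = 0.1 × 10^9/L.

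**The limit evidently intended**

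- 100,000/µL × 1,000 µL per mL = 100,000,000/mL.
- 100,000,000/mL × 1,000 mL per L = 100 × 10^9/L.

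**Size of the discrepancy**

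- 100,000,000/mL ÷ 100,000/mL = 1,000.

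**What a literal reading would admit.** The counts below are illustrative and do not come from the protocol. All lie under 100,000/µL and should be excluded.

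| Platelet count | Same count per mL | Divided by the printed limit of 100,000/mL | Excluded as printed? |
|---|---|---|---|
| 20,000/µL | 20,000,000 | 200 | No |
| 50,000/µL | 50,000,000 | 500 | No |
| 99,000/µL | 99,000,000 | 990 | No |

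**Is it corrected elsewhere?** No. The three statements agree with one another in number and unit, and section 3.6 names the test without giving a limit.

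**Does it reach the statistical design?** No. Neither the sample size in section 5 nor the analysis in section 6 uses this limit.

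**The case against.** There are four serious counter-arguments.

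1. **It may be a reading artefact.** The text at hand was extracted from a PDF, and a µ can be misread as m. The three occurrences are one criterion repeated, so a systematic misread would affect all of them. Against this, mL comes through both as plain text in the synopsis and as typeset mathematics in sections 3.4.2 and 3.10.4, which makes a misread less likely. It does not exclude one. This point stands as a caveat and settles the order of the fix.

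2. **It may be a translation slip.** The English shows signs of translation, such as ISR where INR is meant in section 3.10.4. The text that sites used may differ and cannot be seen here. That is possible, but the protocol under review would still need correcting.

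3. **Nobody would apply it literally.** The criterion is labelled thrombocytopenia and sits under high bleeding risk. A clinician reading a routine blood count would probably apply the limit per µL, and section 3.10.9 offers a helpline for eligibility questions. This largely stands, and it is why the consequence is modest. It does not make the printed limit right.

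4. **The platelet limit is not the main safeguard.** Section 3.10.4 says that in the phase I patients who bled, "laboratory tests that evaluate coagulation (platelet count and levels of coagulation factors) were not altered", and it attributes the bleeding mainly to metastases. Separate items exclude metastatic solid tumours and known malignancy of the central nervous system, and the INR limit still works. This stands too: the phase I bleeding is not evidence that the platelet limit carries the mitigation.

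**Conclusion.** The point holds as a minor eligibility and safety correction. On the text at hand, criterion 3k is wrong by a factor of 1,000 in all three places, and its platelet part does not meet section 8.4's own description of clear and specific criteria. Nothing in the sample size, alpha or primary analysis changes.

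The conclusion rests on three assumptions:

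- The source PDF prints mL as the extracted text does. This is likely but unverified.
- The intended limit is 100,000/µL. The number and the label make this evident, but the protocol does not state it.
- Counts as low as 100/µL are practically never seen in outpatients. This is general laboratory knowledge and is not taken from the protocol.

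The protocol gives no figure for how many patients could be affected. The number is probably small, because sites would likely read the limit per µL.

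**What to change.** 1. Look at the source PDF. If it prints µL, nothing needs changing.
2. If it prints mL, change the limit to <100,000/µL (100 × 10^9/L) in the synopsis, section 3.4.2 and section 3.10.4.
3. Have the clinical lead confirm that this is the intended value.
4. Make sure that any eligibility check, on paper or electronic, uses the same unit.

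The cost is one look at the source and a one-unit edit in three places, with no change to the design or the analysis.
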